## Abstract

**Background::**

Labor pain is one of the most intense pains experienced by women, which leads to an increase in the number of women opting to undergo a cesarean delivery. Pharmacological and nonpharmacological analgesia methods are used to control labor pain. Epidural analgesia is the most commonly used pharmacological analgesia method. However, it may have side effects on the fetus and the mother. Light-emitting diode (LED) photobiomodulation is an effective and noninvasive alternative to pharmacological methods.

**Objectives::**

To evaluate the effects of LED photobiomodulation on analgesia during labor.

**Methods::**

In total, 60 women in labor admitted to a public maternity hospital will be selected for a randomized controlled trial. The participants will be randomized into 2 groups: intervention group [analgesia with LED therapy (n = 30)] and control group [analgesia with bath therapy (n = 30)]. The perception of pain will be assessed using the visual analogue scale (VAS), with a score from 0 to 10 at baseline, that is, before the intervention. In both the groups, the procedures will last 10 minutes and will be performed at 3 time points during labor: during cervical dilation of 4 to 5 cm, 6 to 7 cm, and 8 to 9 cm. At all 3 time points, pain perception will be evaluated using VAS shortly after the intervention. In addition, the evaluation of membrane characteristics (intact or damaged), heart rate, uterine dynamics, and cardiotocography will be performed at all time points.

**Expected outcomes::**

The use of LED photobiomodulation will have an analgesic effect superior to that of the bath therapy.

## Introduction

1

Labor pain is one of the most severe and agonizing events in the life of a woman.^[1–3]^ In previous studies, approximately 41% of women have reported that the high level of pain during natural labor and the fear of pain were the most important reasons for choosing a cesarean section.^[4,5]^ Although pain is a common phenomenon during labor,^[6]^ analgesia for pain relief during labor may be necessary to ensure that labor occurs as naturally as possible,^[7]^ thus benefiting the fetus and the mother.

Labor pain can be controlled by pharmacological and nonpharmacological methods.^[1,4,6,7]^ The use of drugs is the most common method, particularly epidural analgesia.^[8,9]^ However, pharmacological methods may have side effects on the fetus and the mother.^[8,9]^

The administration of epidural analgesia interferes with the secretion of hormones involved in labor, such as oxytocin, prostaglandin-F2a, and β-endorphin;^[6,10,11]^ this interference increases the risk of side effects, such as hypotension, delays the progress of labor, and increases the need for cesarean delivery.^[6,12,13]^ The concern regarding the side effects of pharmacological methods and the philosophy of encouraging vaginal delivery have promoted the discussion pertaining to the existing nonpharmacological methods.

Nonpharmacological alternatives that have been shown to be effective in pain relief include Swiss ball exercises and the hot bath therapy.^[14–18]^ The authors of a systematic review have reported that the hot bath therapy reduced pain in women with a cervical dilation of 8 to 9 cm and therefore reduced the need for pharmacological analgesia.^[14,19]^ The authors emphasized that nonpharmacological methods are beneficial and presented few side effects and contraindications. Furthermore, nonpharmacological interventions are noninvasive and favor the active participation of the mother during labor.^[14,19]^

Therefore, finding analgesic alternatives using effective nonpharmacological methods is an interesting challenge. Photobiomodulation is a noninvasive nonpharmacological intervention used for pain management in different areas of health sciences, such as orthopedics, physical therapeutics, dentistry, etc.^[20–23]^ Photobiomodulation therapy comprises the use of radiation sources, such as laser and light-emitting diodes (LEDs), for the application of nonionizing light; these radiations produce physiological benefits, such as increased microcirculation and ATP synthesis and decreased reactive oxygen species production.^[20–23]^

The analgesic effect of photobiomodulation occurs through the reabsorption of exudates, the elimination of algogenic substances, and via changes in the electrical conduction of the stimulus by maintaining the ionic gradient on both sides of the cell membrane, thereby avoiding or reducing depolarization. The effects of LED therapy on pain management, including the increase in blood flow and relaxation of spasms, have attracted the attention of professionals from different health sectors.^[24]^

The use of LED improves acute orthopedic conditions, such as sprains,^[24–26]^ postsurgical pain, cervical injury,^[27]^ upper and lower back pain, neck pain, and fibromyalgia.^[27–32]^ Because of the broad effects of photobiomodulation, LED therapy may be used as a nonpharmacological and noninvasive alternative for managing pain during labor and may provide comfort to the woman without producing any side effects.

The objective of this protocol is to evaluate the effect of LED photobiomodulation on pain management during natural labor compared with that of bath therapy. The second objective is to evaluate the fetal conditions at birth and in the first hours of life following LED photobiomodulation.

## Methods

2

### Study design

2.1

This randomized controlled trial will be conducted at the maternity ward of a public hospital in São Paulo, state of São Paulo, Brazil. In total, 60 uniparous or multiparous women who request analgesia during labor will participate in the study.

This study complies with the ethical guidelines in human research and was approved by the Research Ethics Committee of the Mandaqui Hospital (São Paulo, Brazil) under Opinion number 2.47.650 and has been registered in Clinical Trials under Protocol No NCT03496857. This is a randomized controlled clinical study; for the purpose of greater transparency and quality of the research, Table 1 summarizes the enrollment, intervention, and assessment schedule, all of which are in accordance with the SPIRIT (Standard Protocol Items: Recommendations for Interventional Trials) recommendations.

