**Table 1 T1:**
[figure not shown]
Schedule of enrolment, interventions, and assessments of treatments.

The participants will be randomized into 2 groups: intervention group [analgesia with LED therapy (n = 30)] and control group [analgesia with bath therapy (n = 30)]. The perception of pain will be evaluated using the visual analogue scale (VAS) with a score from 0 to 10 at baseline, that is, before the intervention. In both the groups, the procedure will last 10 minutes at each of 3 time points during labor: cervical dilation of 4 to 5 cm, 6 to 7 cm, and 8 to 9 cm.^[33]^ At the 3 time points, the level of pain will be assessed using VAS shortly after the intervention. Pharmacological analgesia will be promptly performed whenever necessary; in these cases, the participant will be excluded from the study and replaced with another consecutive participant.

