### Participants

2.3

The study participants will be women aged >18 years, who are expected go into natural labor in the Maternity Hospital of Mandaqui. The inclusion criteria for the study will be as follows: women who request analgesia during labor; nulliparous and multiparous women; women with term gestation; women without previous diseases, including diabetes, neurological diseases, and metabolic diseases; and women in whom it is possible to evaluate fetal vitality during analgesia.

The exclusion criteria will be as follows: women whose labor is induced with medications; women who request drug analgesia during labor; and women who undergo cesarean delivery.

The participants will be recruited on admission at the maternity hospital and will be randomized in the 2 study groups after clarifying regarding the study objectives and obtaining their informed consent.

The sample size has been estimated using the difference in means in the score of the VAS from a study that evaluated analgesia during labor.^[34]^ The difference in the mean VAS score between the groups was set as 2 (standard deviation: 1.6). The minimum number of participants considering a power of 80% and level of significance of 5% was 28, and the minimum number of participants per group considering possible exclusions was 30.

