### Randomization

2.4

The patients will be distributed into the 2 groups by performing block randomization (n = 6) at a ratio of 1:1 according to a code generated by the SPSS software version 20.0 for Windows (IBM Corporation, Armonk, NY).

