### Data analysis

2.7

The distribution of the VAS scores will be analyzed, and the continuous variables with normal data distribution will be compared using the *t* test and expressed as mean ± standard deviation. The categorical variables will be analyzed using the *χ*^2^ test or Fisher exact test. Non-normal data will be analyzed using the Mann–Whitney *U* test. All analyses will be performed using the statistical software SPSS version 20.0 for Windows (IBM Corporation, USA) at a level of significance of 5%.

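### Sections 2.1 and 2.3 describe different eligible populations by parity and must be reconciled; adjusting for parity is an optional gain in precision

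*Protocol article*

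**What the plan says.** Section 2.1 (Study design) describes the sample in one sentence: "60 uniparous or multiparous women who request analgesia during labor will participate in the study".

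Section 2.3 (Participants) lists among the inclusion criteria "nulliparous and multiparous women; women with term gestation". The exclusion criteria in the same section are "women whose labor is induced with medications; women who request drug analgesia during labor; and women who undergo cesarean delivery"; parity is not among them.

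Section 2.4 (Randomization) specifies "block randomization (n = 6) at a ratio of 1:1" and names no stratification factor. Section 2.7 (Data analysis) states that "continuous variables with normal data distribution will be compared using the *t* test", with the Mann–Whitney U test for non-normal data, and names no covariate. Section 2.1 plans 30 women per arm and a VAS score before the intervention. The sample size paragraph in section 2.3 gives the planning values: "The difference in the mean VAS score between the groups was set as 2 (standard deviation: 1.6".

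**The concern.** A uniparous woman has given birth once; a nulliparous woman has not given birth. Section 2.1 therefore describes a sample of women with a previous birth, while section 2.3 opens the trial to first-time mothers. Both are current methods text about the same 60 women. A reader of section 2.1 alone would conclude that first-time mothers were not studied; a reader of section 2.3 would conclude the opposite. The population to which the result applies is therefore unclear.

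If both groups are enrolled, a second and lesser question follows. Parity might be related to pain scores and to the course of labour, although the document gives no figure for either. With 30 women per arm, unstratified blocks and an unadjusted test, a chance difference in parity between the arms is neither prevented nor accounted for.

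**Working it through.** **1. Eligibility, side by side**

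| Place | Parity groups named | First-time mothers? |
|---|---|---|
| 2.1 Study design | uniparous, multiparous | not included, read literally |
| 2.3 Inclusion criteria | nulliparous, multiparous | included |
| 2.3 Exclusion criteria | parity not mentioned | no restriction |

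No other section mentions parity. The two statements cannot both be literally right, and the text does not say which prevails.

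**2. Size of a chance parity imbalance**

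The plan states no figure on this point, so there is none to reproduce. Inputs from the protocol: 30 per arm (2.1), SD 1.6 and target difference 2 (2.3). Assumed, because the document gives neither: the nulliparous share p (0.3 to 0.5) and the mean VAS difference between parity groups (0.5 to 1.5 points).

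SD of the between-arm difference in the nulliparous proportion = √(2p(1−p)/30):
- p = 0.5: √(2 × 0.25/30) = 0.129, or 12.9 percentage points
- p = 0.3: √(2 × 0.21/30) = 0.118, or 11.8 percentage points

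The probabilities below are exact, with the number of nulliparous women in each arm taken as independent Binomial(30, p). A 20-point difference is 0.20 × 30 = 6 women.

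| Assumed p | At least 20 points (6 or more women) | More than 20 points (7 or more women) |
|---|---|---|
| 0.3 | 12.0% | 6.6% |
| 0.4 | 14.7% | 8.6% |
| 0.5 | 15.5% | 9.2% |

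A normal approximation without continuity correction at p = 0.5 gives 2 × (1 − Φ(0.20/0.129)) = 12%. That falls between the two exact values and should not be quoted for either event.

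**3. Effect on the VAS comparison**

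Shift in the estimate = imbalance × parity effect:
- 0.20 × 0.5 = 0.10
- 0.20 × 1.5 = 0.30

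Standard error of the difference in means = 1.6 × √(2/30) = 0.41. The shift is therefore 0.10/0.41 to 0.30/0.41, about a quarter to three quarters of one standard error. Against the target difference it is 0.10/2 to 0.30/2, or 5% to 15%.

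**The case against.** On eligibility, the case for leaving the text alone is that section 2.3 is the formal criteria list and section 2.1 only a summary. A recruiter working from the list would enrol first-time mothers. Both sentences pair a low-parity term with the multiparous group, so both may have been meant as any parity, with the term in section 2.1 a slip. This is plausible and makes the practical risk small. It remains an inference: the document does not say so, and the sections still need to agree.

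On parity in the design and analysis, a reader might infer that the absence of stratification or adjustment is a defect, or that it biases the result. The document does not support either reading:
- It promises no parity stratification or adjustment, so nothing is contradicted. Naming both parity groups in the eligibility list may only show that the trial is open to all; term gestation is named there too.
- A 1:1 block-randomised comparison with an unadjusted test is valid. Imbalance is as likely to favour one arm as the other and averages zero over randomisations.
- If the planning SD of 1.6 comes from women of mixed parity, variation due to parity is already inside it and so inside the standard error.
- Covariates may be settled in an analysis plan that is not shown.

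All of this stands. What remains is a question of precision. One practical point is left: an analysis plan can add a covariate later, but stratification of the blocks has to be fixed before allocation.

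**Conclusion.** The eligibility contradiction is real and follows from the text alone, with no assumption needed. It is minor in practice, because the inclusion list would probably govern, but it leaves the study population ambiguous. The document does not establish which population was intended, and this point does not choose one.

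The parity adjustment is optional and corrects no error. Even in the unlucky case of a 20-point imbalance, the shift is less than one standard error and small beside the target difference. That judgement depends on the assumed nulliparous share and the assumed parity effect, and on applying the protocol's SD of 1.6 to this population. It would also be wrong to infer that parity is known to alter labour length or to cause missed dilation windows in this trial; the document has no data on either.

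**What to change.** **Needed.** Make sections 2.1 and 2.3 name the same parity groups. Cost: one sentence.

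**Optional, if both nulliparous and parous women are enrolled.**
- Replace the unadjusted VAS comparison with a linear model containing treatment group, baseline VAS and parity. Baseline VAS is already collected and parity is known at admission, so the cost is two model terms and no new data.
- Consider stratifying the blocks of 6 by parity. Cost: two allocation lists instead of one. The downside is one or two incomplete blocks. Each can leave the arms at most 3 women apart, so the worst case over two strata is a difference of 3 + 3 = 6, or 33 against 27 among 60 women, setting replacements aside.

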**Table 1 T1:**
[figure not shown]
Schedule of enrolment, interventions, and assessments of treatments.

The participants will be randomized into 2 groups: intervention group [analgesia with LED therapy (n = 30)] and control group [analgesia with bath therapy (n = 30)]. The perception of pain will be evaluated using the visual analogue scale (VAS) with a score from 0 to 10 at baseline, that is, before the intervention. In both the groups, the procedure will last 10 minutes at each of 3 time points during labor: cervical dilation of 4 to 5 cm, 6 to 7 cm, and 8 to 9 cm.^[33]^ At the 3 time points, the level of pain will be assessed using VAS shortly after the intervention. Pharmacological analgesia will be promptly performed whenever necessary; in these cases, the participant will be excluded from the study and replaced with another consecutive participant.

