### Objectives of the study

2.2

Primary objective: To evaluate the effect of LED photobiomodulation on analgesia during labor as an alternative nonpharmacological intervention.

Research hypotheses:

Hypothesis 0 (null): the use of LED photobiomodulation exerts an analgesic effect similar to that of the bath therapy.

Hypothesis 1: the use of LED photobiomodulation exerts an analgesic effect superior to that of the bath therapy.

Hypothesis 2: the use of LED photobiomodulation exerts an analgesic effect inferior to that of the bath therapy.

Secondary objective: To evaluate fetal conditions using cardiotocography and the Apgar score in the first and fifth minutes after birth, and the level of satisfaction with the experience of childbirth using a questionnaire.

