#### Intervention group: LED therapy

2.5.1

LED therapy sessions will be held in the prelabor room. The patient who will undergo analgesia and the professional responsible for placing the LED plate on the patient's back, between T10 and L2, will be present at the time of the intervention. The LED plate will be covered with clear disposable polyvinyl chloride to avoid cross-contamination and ensure hygiene. During the interventions, the patient will be allowed to choose the position that is the most comfortable for her.

Three 10-minute LED applications will be performed when the patient has a cervical dilatation of 4–5, 6–7, and 8–9 cm. Data on the level of pain, characteristics of the membrane (intact or damaged), heart rate, cardiotocography, and uterine dynamics will be collected after each intervention.

The LED device used is SportLux (Cosmedical, São Paulo, Brazil), and the dose parameters are shown in Table 2.

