### Control group: bath therapy

2.6

The method of analgesia with the bath therapy will be performed using a hot shower at 37°C for 10 minutes. After showering the entire body or the back for 5 minutes, the participants will be allowed to direct the water flow to any area of the body that feels the most comfortable and to adjust the temperature themselves for improved comfort. Bath therapy will be performed at 3 time points during labor: at cervical dilatation of 4–5 cm, 6–7 cm, and 8–9 cm. Data on the level of pain, membrane characteristics (intact or damaged), heart rate, cardiotocography, and uterine dynamics will be collected after the bath therapy by performing the same measurements used in the intervention group.

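### As the text describes it, VAS is taken once before treatment and then only after each session, so within-arm change across the second and third sessions cannot be told apart from labor progress or carry-over

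*Protocol article*

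**What the plan says.** The abstract and section 2.1 of the protocol article give the same timing for pain scores. One VAS score is taken "at baseline, that is, before the intervention". Treatment is then repeated: "In both the groups, the procedure will last 10 minutes at each of 3 time points during labor", namely at 4–5, 6–7 and 8–9 cm of dilation. For the later scores, section 2.1 says: "At the 3 time points, the level of pain will be assessed using VAS shortly after the intervention".

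The sections on each arm agree. In section 2.5.1 (LED), level of pain is among the data that "will be collected after each intervention". In section 2.6 (bath), the data "will be collected after the bath therapy by performing the same measurements used in the intervention group".

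The question under test is a comparison of arms. The null hypothesis in section 2.2 is that "the use of LED photobiomodulation exerts an analgesic effect similar to that of the bath therapy", with alternatives in both directions. Section 2.7 plans two-group tests: the t test, or Mann–Whitney for non-normal data. No passage defines the effect as a change from baseline.

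Section 2.1 refers to Table 1 for the assessment schedule. Its contents were not available for this check.

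**The concern.** Treatment comes as three separate sessions while labor advances. For the first session there is a score before and a score after. For the second and third, the only score from before treatment belongs to an earlier stage of labor. A drop or rise from that score to the one taken after a later session mixes three things: the relief from that session, what remains of earlier sessions, and the change in pain as labor proceeds. No untreated arm supplies the last of these.

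This matters most if the arms come out alike. Equal post-session scores are compatible with two treatments that both relieve pain at that stage and with two that both do nothing. Section 3 presents the trial's main contribution as an effective intervention, so readers will ask which of the two it is. Scores not taken before the later sessions cannot be recovered afterwards.

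**Working it through.** The plan states no figure on this point, so there is none to reproduce. The sample-size statement in section 2.3 supplies only the SD of 1.6 and the 30 women per group used below.

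**Algebra.** For one arm at a later stage, let B be the mean baseline score, r the rise in pain since baseline that would occur without treatment, c the carry-over relief from earlier sessions and s the relief from the current session.

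- Score just before the session (not described in the text): B + r − c
- Score just after the session: B + r − c − s
- Baseline minus post-session score: c + s − r

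The last line is the only within-arm change the described scores allow. It is one observed quantity with three unknowns.

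Between arms, with L for LED and B for bath as subscripts, randomisation makes the baseline mean and r equal in expectation at a given stage. Then:

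- Post-session difference (bath minus LED): (c_L + s_L) − (c_B + s_B)

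The rise r cancels. This contrast estimates the relative effect of all sessions up to that stage, not of the latest session alone.

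**If the arms look alike.** Suppose both have a mean of 6 at baseline and 6 after the third session (assumed values). A rise of 2 with relief of 2 gives 6 + 2 − 2 = 6. A rise of 0 with relief of 0 gives 6 + 0 − 0 = 6. The described scores cannot distinguish these.

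**Simulation.** Assumptions: 30 women per arm; baseline mean 6; between-woman SD 1.1 and residual SD 1.16, so the total SD is √(1.1² + 1.16²) = √2.5556 ≈ 1.60; a true total relief of 2 points in both arms at the third session, so the true between-arm difference is 0; a rise common to both arms; 4,000 repetitions per row; two-sample t test at 5%.

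| Assumed rise in pain | Mean within-arm drop from baseline (true relief 2) | Between-arm difference (true value 0) | Type I error |
|---|---|---|---|
| 0 | 1.99 | 0.010 | 5.45% |
| 1 | 0.99 | 0.010 | 4.80% |
| 2 | 0.00 | 0.010 | 5.03% |
| 3 | −1.00 | 0.006 | 4.80% |

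The within-arm column follows 2 − r, as the algebra predicts. The other two columns do not move with r. The simulation error of the difference is 1.6 × √(2/30) / √4000 ≈ 0.0065, and that of the type I error is √(0.05 × 0.95 / 4000) ≈ 0.34 percentage points, so all departures from 0 and 5% are within sampling noise.

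**What pre-session scores would add.** Pre minus post within a session is s, less any change in pain over the 10 minutes that would have happened anyway. The between-arm difference in this change is s_L − s_B. It omits c_L − c_B, so it understates LED's total advantage if LED has the larger carry-over.

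**The case against.** The strongest reply is that the trial does not ask the within-arm question. Its hypotheses and tests compare LED with bath, both arms are treated and scored at the same dilation stages, and comparing one whole regimen with the other at each stage is a legitimate target. That stands. It is why this is a point about interpretation and not about validity.

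The reply also holds that pre-session scores are only a partial cure. With no untreated arm, a drop across a session could reflect contraction timing or regression to the mean, and carry-over would still shrink the difference in change. That stands too, so the added analysis can only be supportive.

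Three stronger readings are tempting, and the documents do not support them:

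- **The main comparison is confounded by labor progress.** It is not, because the rise is common to the randomised arms and cancels.
- **The extra scores would sharpen the primary comparison.** The article gives no pre–post correlation from which to judge this. In any case, later pre-session scores arise after treatment has started and should not be adjusted for in that comparison.
- **The extra scores would rescue information on women who need drug analgesia.** Section 2.1 excludes and replaces those women, so their scores would leave the analysis with them. That is a separate matter.

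Finally, Table 1 may list scores before each session. The text on its own reads most naturally as one baseline score, but this cannot be settled without the table.

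**Conclusion.** The point holds in limited form. On the text as written, the effect of the second and third sessions within an arm is not identifiable: with a true relief of 2 points, the apparent change runs from a 2-point drop to a 1-point worsening as the assumed rise in pain goes from 0 to 3 points. The range of rise is an assumption, as the article gives no figure for it. The LED-versus-bath comparison of post-session scores is unaffected, provided both arms are scored at the same stages as planned. The consequence is confined to session-level and within-arm statements, and it bites chiefly if the arms look similar. This is an optional improvement and not a defect in the tested comparison, and it is conditional on what Table 1 shows.

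**What to change.** Record VAS immediately before each of the three sessions as well as after it, in the same way in both arms.

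- **Primary comparison:** keep post-session VAS between arms, adjusted for the first pre-treatment VAS, which is already collected. Do not adjust it for the later pre-session scores.
- **Secondary, supportive analysis:** report the between-arm difference in within-session change. State alongside it that carry-over can understate a difference and that, without an untreated arm, a drop is not proof of effect.
- **Text:** if Table 1 already lists pre-session scores, reconcile the abstract and sections 2.1, 2.5.1 and 2.6 with it. In that case no new measurement is needed.

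The cost is two extra VAS marks per woman, which is a small added burden during labor, and one further analysis. The change has to be made before data collection.

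### Women given drug analgesia after randomisation are excluded and replaced, so the VAS comparison is of women who coped in each arm and not of the randomised groups

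*Protocol article*

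**What the plan says.** Under section 2.3 of the protocol article, "The participants will be recruited on admission at the maternity hospital and will be randomized in the 2 study groups", once consent is given. The 10-minute sessions follow at 4–5, 6–7 and 8–9 cm of dilation, and "At the 3 time points, the level of pain will be assessed using VAS shortly after the intervention" (section 2.1).

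Section 2.1, in the text below Table 1, then states: "Pharmacological analgesia will be promptly performed whenever necessary"; "in these cases, the participant will be excluded from the study and replaced with another consecutive participant". Among the exclusion criteria, section 2.3 lists "women who request drug analgesia during labor; and women who undergo cesarean delivery".

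The primary objective (section 2.2) is the effect of LED on analgesia. The secondary objectives are fetal condition by cardiotocography and Apgar score, and satisfaction with the birth. Section 2.7 compares the arms by t test or Mann–Whitney test and names no analysis population. Nothing in the article returns an excluded woman to an analysis.

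**The concern.** Allocation comes first, then treatment, then rescue. Removal is therefore decided after randomisation, by something the treatment can influence. The introduction itself credits the comparator with such an effect: it reports that hot bath therapy lowered pain "and therefore reduced the need for pharmacological analgesia". A woman who needs drugs is, in most cases, one whose pain the allocated method did not control. Dropping her takes a probable high score out of her arm, and her replacement is kept only if she copes.

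Three things are at stake:

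- The VAS difference no longer estimates the effect of allocation. If one arm controls pain worse, it loses more of its worst scores and looks better than it is.
- If women or staff turn to drugs more readily in one arm, a difference can appear where none exists. A shower and an LED plate cannot be mistaken for each other, so equal readiness cannot be presumed.
- The same women drop out of the fetal, Apgar and satisfaction comparisons. Excluding caesarean deliveries has the same structure.

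**Working it through.** **Inputs from the protocol article.** Difference 2, SD 1.6, power 80%, significance 5% (section 2.3); 30 per arm. Both a superior and an inferior alternative are listed (section 2.2), so the test is taken as two-sided. No rescue rate is given.

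**1. Is replacement needed for power?** The per-arm size is n = 2(z₁₋α/₂ + z_power)²(SD/difference)².

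- At 80% power: 2 × (1.960 + 0.842)² × 0.64 = 10.05, so 11 per arm (12 by exact t test).
- The protocol's 28 is not reproduced, either as a total or per arm. It appears as a total (14 per arm) at 90% power: 2 × (1.960 + 1.282)² × 0.64 = 13.5. That is a separate matter.
- Power at 30 per arm: Φ(1.25 × √15 − 1.96) = Φ(2.88) = 0.998, or 0.997 by t test.

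Replacement is not needed to protect power at these inputs.

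**2. Removing the top fraction q of one arm.** For a normal score the mean moves by −SD × φ(z₁₋q)/(1 − q). With SD 1.6:

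- q = 10%: −1.6 × 0.1755/0.90 = −0.31
- q = 20%: −1.6 × 0.2800/0.80 = −0.56
- q = 30%: −1.6 × 0.3477/0.70 = −0.79

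These describe one arm alone. Losses in the other arm offset them in part.

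**3. Gradual rescue (assumed).** There is one latent post-session VAS per woman, normal with SD 1.6 and bath mean 6.5. The rescue probability is 1/(1 + exp(−(VAS − m))), with m = 9, 8 or 7. Rescued women are dropped.

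True benefit of 2 (LED mean 4.5), same m in both arms:

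| m | Rescue, bath | Rescue, LED | Difference among women kept |
|---|---|---|---|
| 9 | 14% | 3% | 1.79 |
| 8 | 26% | 7% | 1.67 |
| 7 | 42% | 15% | 1.55 |

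No true difference (both means 6.5), t test at 30 per arm:

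| Rescue in the two arms | Spurious difference | Type I error |
|---|---|---|
| 14% v 14% | 0 | about 5% |
| 26% v 14% | 0.20 | about 8% |
| 42% v 14% | 0.45 | about 23 to 24% |

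The spurious difference favours the arm with more rescue, whichever arm that is.

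**4. Hard threshold (assumed, harsher).** Bath mean is 7, and every woman above threshold c is rescued. The mean of those kept is μ − SD × φ(a)/Φ(a), with a = (c − μ)/SD.

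- c = 9, true benefit 2. Bath: a = 1.25, 7 − 1.6 × 0.1826/0.8944 = 6.67. LED: a = 2.5, 5 − 1.6 × 0.0175/0.9938 = 4.97. Difference 1.70.
- c = 8: 6.28 − 4.89 = 1.40 (rescue 27% v 3%).
- c = 7: 5.72 − 4.67 = 1.05 (rescue 50% v 11%).
- No true difference, thresholds one point apart: 6.67 − 6.28 = 0.39 (rescue 11% v 27%) or 6.28 − 5.72 = 0.56 (27% v 50%). The t test rejects in about 22% or 52% of trials.

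The two models agree on direction and differ in size.

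**The case against.** The strongest defence is that a journal article condenses a fuller protocol, and that an analysis plan could name an intention-to-treat set. That would answer a complaint about silence. It does not answer a rule stated outright: a woman excluded from the study may have no later data, and no analysis set can recover data never collected.

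Parts of the defence stand. Under the planned benefit the distortion is conservative. With 30 kept per arm, power stays near 99% in the gradual model and about 92% in the harshest threshold case (11% v 50% rescue), so the benefit would still be detected, though underestimated. With no true effect and equal readiness to rescue there is no bias. No passage says that readiness differs by arm, and all the sizes rest on assumed rescue rates.

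A reader might also infer four stronger points that the article does not support:

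- *The two exclusion rules contradict each other.* Section 2.1 turns on drugs being given and section 2.3 on their being requested. Section 2.3 is an eligibility list and may only separate women seeking non-drug relief from women seeking drugs.
- *Recruitment runs until 30 women per arm have completed*, implying 67 to 86 randomised at 10 to 30% rescue (60/0.9 to 60/0.7). The article does not say that a replacement joins the same arm or that 30 completers is the target. Section 2.3 sets 30 with exclusions already allowed for, which sits awkwardly with replacement and should be reconciled.
- *Rescue use will go unreported.* The rule does not bar reporting exclusions and reasons by arm.
- *The rule favours LED.* The direction depends on which arm loses more women.

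**Conclusion.** The point holds for the exclude-and-replace rule in section 2.1 and for the section 2.3 exclusions that can occur after randomisation. As written, the primary VAS comparison is conditional on a post-randomisation sign of treatment failure. This should be corrected before the trial is analysed, and preferably before further women are excluded.

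The size is uncertain. Under the gradual model, a true 2-point benefit is understated by roughly 0.2 to 0.45 points. With no effect and unequal readiness, a false difference of similar size arises, with type I error of about 8 to 24% against a nominal 5%. The hard-threshold model gives larger figures. These are illustrations that depend on rescue rates and models the document does not supply; only the SD and the planned difference are its own.

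**What to change.** 1. In section 2.1, delete exclusion and replacement after pharmacological analgesia. The clinical rule for giving rescue is unchanged.
2. In section 2.3, limit the drug-analgesia and caesarean criteria to events before randomisation. Changing section 2.1 alone would leave them standing.
3. Keep every randomised woman in her allocated group, and continue to record VAS, cardiotocography, Apgar and satisfaction after rescue or caesarean.
4. Pre-state how VAS is handled at time points after rescue or never reached because of caesarean. One option is a worst-rank composite analysed by Mann–Whitney test, with a sensitivity analysis of VAS as observed. Other strategies are acceptable if fixed in advance.
5. Report drug analgesia and caesarean by arm, each with a 95% confidence interval for the difference.

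The cost is protocol and analysis wording, continued recording in rescued women, and one sensitivity analysis. The estimate may be less favourable, and the worst-rank option replaces a mean difference, on which the sample size rests, with a rank comparison. No extra women are needed at the stated inputs: power at 30 per arm is 99.7% for the mean comparison, and about 98 to 99% for the worst-rank composite under the gradual model.
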